# OBJECTIVES

- 1. Primary Objective
- To identify candidate blood and urine biochemical markers that correlate with disease severity as determined by the Modified Hammersmith Functional Motor Scale across a range of type I, type II and type III children with spinal muscular atrophy (SMA).
  1. Secondary Objectives
- To determine if there are biochemical markers from types I-III SMA patients that correlate with SMA type, age at disease onset, 10-meter Timed Walk Test (ambulatory subjects only), pulmonary function, nutritional assessment, SMN protein level, SMN transcript level, or SMN2 copy number.
- To determine if identified candidate biomarkers are associated with the disease state through comparison of SMA specimens with control volunteer specimens.
- To determine if there are potential biochemical pathways that may represent targets for therapeutic intervention in SMA.

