# STUDY MEasurements

- 1. Motor Function Assessment

The Modified Hammersmith Functional Motor Scale (15) provides a tool for evaluation of motor function in pediatric subjects with SMA type II and type III. The Modified Hammersmith Functional Motor Scale will be performed according to the Study Manual of Operations. A score of “0” is acceptable for those unable to perform any of the measurements (e.g., type I SMA subjects). In this study, both control subjects and SMA subjects will undergo the assessment as the scale is being used as the primary outcome. A minimal amount of equipment is required to perform the evaluation and the total duration is ~20 to 30 minutes to complete. Each site will have a clinically trained person performing these evaluations. It is anticipated that for control subjects, the assessment will require a minimum amount of effort and will take approximately 10 minutes to complete.

- 1. 10-meter Timed Walk Test

A 10-meter Timed Walk Test will be performed on all ambulatory SMA subjects and controls according to the Study Manual of Operations. This test compares higher functioning subjects with SMA and control subjects in their ability to walk 10 meters. (16, 17, 18)

- 1. Pulmonary Function

On subjects age >5 years, spirometry will be performed according to the Manual of Operations to measure the maximal volume of air forcibly exhaled from the point of maximal inhalation (forced vital capacity, FVC). The test will be performed 3 times in a sitting position. Subjects unable to sit may perform the FVC in a supine position and document on the appropriate CRF. Subjects who are unable to perform or complete the FVC tests may still participate in the study.

- 1. Triceps Skin Fold Thickness

The measurement of skin fold thickness of the subject’s upper arm will give an estimate of body composition and will be correlated with BMI Z score. Variability of measurement will be decreased by detailed standard procedures in the Manual of Operations and hands-on training.

- 1. Height, Weight and Ulnar Length

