# STATISTICAL CONSIDERATIONS

- 1. Power Calculations

A sample size of 15 Type I, 45 Type II, and 40 Type III SMA cases provides 83% power for the primary outcome of Modified Hammersmith Functional Motor Scale using an elastic net multivariate regression analysis of Modified Hammersmith Functional Motor Scale on composite biomarker sets, at level 0.05, assuming a correlation between observed and theoretical outcomes of 0.75. This power calculation also assumes that 10% of analytes are true biomarkers, a variance of 0.2 for all analytes, with 100 analytes profiled. The power estimate is based on an average of 100 simulated datasets using data available from the original Hammersmith Scale.

The power to detect a mean fold change (MFC) of 1.3 in the key secondary outcome of SMA type, under the same assumptions as above, is 89% for univariate analysis of variance (ANOVA), when the false discovery rate (FDR) is controlled at level 0.10. For multivariate PAM analysis (Prediction Analysis of microarrays), power is 83% to detect a multivariate biomarker set with MFC of 1.2, when the theoretic prediction accuracy is 61%. These power calculations assume monotone identical differences between SMA types, and are based on an average of 100 simulated datasets for ANOVA and 1000 for PAM.

Additionally, the sample size of 100 SMA cases and 20 controls, under the same assumptions as above, provides 92% power to detect a univariate biomarker with a MFC of 1.5 between SMA and control cases (t-test) when the FDR is controlled at level 0.05.

- 1. Statistical Analysis

The primary outcome for this study is the Modified Hammersmith Functional Motor Scale. A score of “0” is acceptable for those unable to perform any of the measurements (e.g., type I SMA subjects). Secondary outcomes include SMA type, timing of symptoms (age of disease onset, age of maximum function), motor milestones, nutritional assessment (height, weight, triceps skin fold thickness, ulnar length, nutritional question), pulmonary assessment (standardized question about level of respiratory support, FVC when ≥ 5 years), SMN protein, SMN transcript and SMN2 copy number. Descriptive statistics (e.g., means, standard deviations, percents) of all outcomes will be calculated for SMA and control cases, as well as by SMA type. The populations will also be described by vital signs, loss of motor function, and age appropriate neurological exam results.

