In order to find disease-specific biomarkers, comparison of biomarkers between SMA and control cases will be performed using regression analysis, controlling for sex and age. Correlations of biomarkers with outcomes will be conducted within SMA cases, as well as in the combined population of SMA and control cases.

To model the correlation of each individual biomarker with the Modified Hammersmith Functional Motor Scale, univariate regression analyses will be performed, controlling for sex and age. Additionally, elastic net multivariate regression (25) will be used to find a composite set of biomarkers that correlates with outcome.

Univariate regression and elastic net multivariate regression will also be used for continuous secondary outcomes (e.g., age of disease onset, height, weight). For categorical outcomes (e.g., SMA type), analysis of variance (ANOVA), controlling for sex and age, will be performed to discover individual biomarkers that vary by outcome. Likewise, PAM (Prediction Analysis of microarrays) (26) will be used to try to find a composite set of biomarkers that varies by outcome.

In all analyses a p-value ≤ 0.05 will be considered statistically significant. The false discovery rate (27) will also be controlled. If there is an extensive amount of missing data, or data appears not to be missing completely at random, then multiple imputations will be considered. Standard statistical software packages (e.g., SAS) will be used.

- 1. Interim Analysis

No interim analysis for safety or efficacy will be performed during this study.

- 1. Potential Risks and Benefits

Potential risks to study subjects are minimal. Blood will be drawn in volumes that are approximately half (or less than half) of the maximum blood draw allowed for children (by weight) (28) (29). SMN2 copy number will be genotyped from DNA specimens for all cohorts. SMN1 gene analysis will only be done on those control subjects with no genetic relationship to SMA children. SMA subjects will be pre-diagnosed and therefore no further risks are anticipated from a genetic point of view. The control subjects may opt out of the DNA portion (SMN1 gene analysis) of the study. The control subject’s risk is that the study does not benefit the individual directly.

Potential benefits are that study subjects will benefit from the satisfaction that they are participating and contributing to SMA research.

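### Section 11.2 correlates biomarkers with motor score in SMA and controls combined, without a disease-status term or a stated deciding population, so a pure case-control difference can pass as a severity marker

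*Protocol*

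**What the plan says.** Section 11.2 (Statistical Analysis) sets the populations: "Correlations of biomarkers with outcomes will be conducted within SMA cases, as well as in the combined population of SMA and control cases". For MHFMS, "univariate regression analyses will be performed, controlling for sex and age", and an elastic net is added to find a composite set. No SMA/control term is named, and neither population is given precedence in that section.

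Section 7.1 has controls take the MHFMS because it is the primary outcome, and expects that "for control subjects, the assessment will require a minimum amount of effort". Section 2.1 confines the primary objective to severity "across a range of type I, type II and type III children with spinal muscular atrophy (SMA". The matching power statement in 11.1 counts SMA children only: "A sample size of 15 Type I, 45 Type II, and 40 Type III SMA cases provides 83% power". Association with disease state is a separate secondary objective (2.2) and has its own SMA-versus-control regression in 11.2.

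**The concern.** The combined correlation mixes two questions that the objectives keep apart: whether a marker tracks severity among affected children, and whether it separates affected from healthy children. Controls differ from SMA children on MHFMS by design. With only sex and age in the model, a shift between cases and controls therefore produces a correlation with MHFMS even if the marker carries no severity information. Adjusting for sex and age does not help, because controls are recruited to match the SMA cohorts on both.

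The output of this pilot is a candidate list meant to lead towards pharmacodynamic or surrogate use. If the combined set may nominate candidates, markers of merely being affected can enter the list as severity markers. Secondary objective 2 then checks the identified candidates against controls, so the same shift would both select and confirm them.

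**Working it through.** **1. The nearest stated figure.** No figure in the protocol addresses the combined correlation. The closest is the case-control power: "the sample size of 100 SMA cases and 20 controls, under the same assumptions as above, provides 92% power", for a mean fold change (MFC) of 1.5, "when the FDR is controlled at level 0.05". With SD = √0.2, 100 analytes of which 10 are true, and a two-sided t-test, I obtain:
- natural-log fold change: 78% (Benjamini-Hochberg simulation) to 81% (closed form)
- raw difference of 0.5: 95-96%
- log2: 99%

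The stated 92% lies between these. The protocol does not give the scale, so the figure is not reproduced but is not shown to be wrong. Nothing below depends on it.

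**2. Inputs.**
- From 11.1: 15/45/40 SMA children, 20 controls, analyte variance 0.2, 100 analytes, MFC 1.5.
- From 11.2: p<=0.05, covariates sex and age.
- Assumed, because the protocol gives no MHFMS distribution: score as a share of the maximum; type I = 0; controls = 1; mean (SD) for types II and III of 0.30 (0.15) and 0.75 (0.20) base, 0.15 (0.10) and 0.55 (0.20) low, 0.45 (0.20) and 0.90 (0.10) high.
- Also assumed: natural-log scale, and a marker shifted in controls only, with zero association within SMA.

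**3. Induced correlation by formula.** Let q = 20/120 be the control share, so q(1−q) = 0.1389. Let δ = ln 1.5 = 0.405, and let D be the control mean minus the SMA mean on MHFMS.

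- Covariance = q(1−q)·δ·D
- Marker variance = 0.2 + q(1−q)·δ² = 0.2 + 0.1389 × 0.1644 = 0.2228
- MHFMS variance = (1−q)·Var(SMA) + q(1−q)·D²

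Base case:
- SMA mean = 0.45 × 0.30 + 0.40 × 0.75 = 0.435, so D = 0.565.
- Var(SMA) = within 0.0261 + between 0.0763 = 0.1024.
- MHFMS variance = 0.8333 × 0.1024 + 0.1389 × 0.3192 = 0.1297.
- Covariance = 0.1389 × 0.405 × 0.565 = 0.0318.
- r = 0.0318 / √(0.2228 × 0.1297) = 0.187.
- Fisher's z with two covariates: atanh(0.187) × √(120 − 2 − 3) = 2.03, so P(p<=0.05) is about Φ(2.03 − 1.96) = 0.53.

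**4. Simulation.** 1,500 trials per setting; MHFMS regressed on each analyte with sex and age; MFC 1.5.

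| Assumed MHFMS | D | r, formula | r, simulated | p<=0.05 | BH at 0.05 |
|---|---|---|---|---|---|
| Base | 0.565 | 0.187 | 0.193 | 56% | 11% |
| Low | 0.7125 | 0.238 | 0.238 | 75% | 31% |
| High | 0.4375 | 0.146 | 0.149 | 36% | 3% |

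Restricting to SMA, or adding a disease-status term, gives mean r of about 0 and rejection of about 5% in every row. A separate simulation under its own assumed distributions gave about 55% (36-78%).

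**5. Other shift sizes** (base, range over the three distributions):

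| MFC | p<=0.05 | BH at 0.05 |
|---|---|---|
| 1.1 | 8% (7-10%) | below 1% |
| 1.2 | 16% (11-23%) | about 1% |
| 1.3 | 28% (19-41%) | 2% (1-5%) |
| 2.0 | 94% (75-99.5%) | 68% (26-94%) |

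**6. Elastic net.** A small run (105 datasets, base distribution, MFC 1.5, 10-fold cross-validation, mixing 0.5, no sex or age terms) selected 53% of the shifted analytes in the combined set, against 14% of the null ones. In SMA only it selected 5% of each. This is indicative only.

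**The case against.** The strongest reply is that the primary objective is safe. The sentence in 11.2 also plans the within-SMA analysis, and the objective and the 83% power both rest on SMA children. That stands: a reader might infer that the primary analysis is broken, and the documents do not support this. What is missing is a statement in 11.2 that the within-SMA result decides.

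Second, 11.2 also controls the false discovery rate, so the 55% must not be quoted alone. This stands for the size: 11% (3-31%) at MFC 1.5 if the level is 0.05. Section 11.2 names no level, and 11.1 uses both 0.05 and 0.10. But the procedure is no cure. In the combined population the null really is false for such a marker, so it counts as a true discovery.

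Third, one might infer that every case-control difference will be reported as a severity finding, or that all outcomes are inflated. Neither follows. Small shifts are rarely declared. Age at onset is collected for SMA children only (6.4), and SMA type does not apply to controls, so a combined correlation there is undefined rather than inflated.

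Fourth, this is an exploratory pilot with later validation, and showing both analyses side by side is legitimate. Hence deleting the combined analysis would be a preference. Later validation does not correct the candidate list that this study hands on.

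**Conclusion.** The concern holds in a limited form. As 11.2 is worded, the combined analysis can present a pure SMA-versus-control marker as one that correlates with MHFMS, and the section does not say that such a result does not identify a severity marker. The same applies to other outcomes that controls have and on which they differ from SMA children.

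The direction of the problem follows from the design. Its size does not: it rests on the assumed MHFMS distributions, on controls scoring at the maximum (supported by 7.1 but not stated there), and on the natural-log scale. This is more than detail left to an analysis plan, because the protocol itself fixes the populations and the covariates.

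**What to change.** In 11.2, state that severity markers are identified from the within-SMA analysis, whether by univariate regression, elastic net, ANOVA or PAM. If the combined correlations are kept, label them supportive, add an SMA/control term so that the slope is estimated within groups, and limit them to outcomes defined in controls (not age at onset, age of maximum function or SMA type).

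The cost is a short wording change, with no change to data or sample size. The downside is that markers appearing only in the combined set no longer count as severity markers. They remain covered by the SMA-versus-control comparison already in 11.2.

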# PROTOCOL ADMINISTRATION

- 1. Good Clinical Practices

The study will be conducted in accordance with the principles of Code of Federal Regulations, Title 45, Public Welfare Department of Health And Human Services, Part 46 Protection Of Human Subjects (revised June 23, 2005) (30), ICH Good Clinical Practice (CPMP/ICH/135/95; January 1997) and applicable regulatory requirements. Essential clinical documents will be maintained to demonstrate the validity of the study and the integrity of the data collected. Master files will be established at the beginning of the study, maintained for the duration of the study and retained according to the appropriate regulations (31).

- 1. Ethical Considerations

The study will be conducted in accordance with ethical principles founded in the Declaration of Helsinki. (32) The IRB/IEC will review all appropriate study documentation in order to safeguard the rights, safety and well being of the subjects. The study will only be conducted at sites where IRB/IEC approval has been obtained. The protocol, informed consents, advertisements (if applicable), written information given to the subjects, safety updates, annual progress reports and any revisions to these documents will be provided to the IRB/IEC by the investigator.

- 1. Protocol Compliance

The investigator will conduct the study in compliance with the protocol and will obtain approval by their local IRB/IEC. Modifications to the protocol should not be made without agreement of both the investigator and the Sponsor. Changes to the protocol will require written IRB/IEC approval prior to implementation, except when the modification is needed to eliminate an immediate hazard(s) to subjects or if the change(s) involves only logistical or administrative aspects of the study. The IRB/IEC may provide, if applicable regulatory authority (ies) permit, expedited review and approval/ favorable opinion for minor change(s) in ongoing studies that have the approval of the IRB/IEC.

When immediate deviation from the protocol is required, the investigator will contact the Sponsor, if the circumstances permit, to discuss the planned course of action. Any departures from the protocol must be fully documented in the source documentation.

- 1. Subject Confidentiality

In order to maintain subject confidentiality the study will take the following steps:

- Case report forms, study reports and communications will identify the subject by the assigned subject number. Participant names, initials, social security numbers or hospital ID numbers will not be used.
- The investigator will grant monitor(s) and auditor(s) from the Sponsor, the Coordinating Center, the IRB/IEC and regulatory authority(ies) access to the subject’s original medical records for verification of data gathered on the case report forms and auditing of the data collection process.
- All specimens collected will be labeled only with the date of collection, random barcode and study-specific subject ID number.
- The subject’s confidentiality will be maintained and will not be made publicly available to the extent permitted by the applicable laws and regulations.
- Shared datasets (see section 12.8 Publication and Use of Information) will not include patient identifiers, participant initials or dates of birth.
- At clinic sites, hard copy data collection forms will be stored in locked filed cabinets or locked rooms.
- Confidentiality of computerized data will be preserved by means of unique passwords and identification checks. Access to the ADEPT web-based data management system is password controlled and passwords must be changed every 90 days. The system includes an automatic timeout and will terminate the session automatically if not activity has occurred for 30 minutes.
  1. Specimen Retention

Specimens collected may be stored for up to 10 years following the completion of the study and will be destroyed after that time. Specimen destruction will be documented. In addition, specimens can be destroyed at any time at the subject’s or subject’s parents/guardians request.

- 1. Record Retention

An investigator is required to prepare and maintain adequate and accurate case histories that record all observations and other data pertinent to the investigation on each individual for both SMA and control cohorts in the investigation. Case histories include the case report forms and supporting data including, for example, signed and dated consent forms and medical records including, for example, progress notes of the physician, the individual's hospital chart(s), and the nurses' notes. The case history for each individual shall document that informed consent was obtained prior to participation in the study. An investigator shall retain records required to be maintained under this part for a period of 10 years following the study publication. Should investigators be unable to continue maintenance of subject files for the above duration, the Sponsor will assist in this regard.

- 1. Study Termination by the Sponsor

This study may be prematurely terminated if, in the opinion of the investigator or Sponsor, there is sufficient reasonable cause. Written notification documenting the reason for such a termination will be provided to the investigator or Sponsor.

Circumstances that may warrant termination include, but are not limited to:

- Determination of unexpected, significant or unacceptable risk to the subject.
- Failure to enter subjects at an acceptable rate.
- Insufficient adherence to protocol requirements.
- Insufficient complete and/or evaluable data.
  1. Publication and Use of Information

The Spinal Muscular Atrophy Foundation (SMA Foundation, “Sponsor”) is sponsoring this pilot study to stimulate the identification and development of biomarkers with the sensitivity and specificity for use as validated pharmacodynamic markers and/or surrogate endpoints. To that end, the SMA Foundation has agreed to make data generated during this study available to qualified investigators in the field after a period of confidentiality through a recognized data repository program. It is anticipated that this time period will coincide with the submission of the primary study-wide results manuscript as driven by the Protocol Committee and the sponsor. The shared data set will include de-identified subject data. Dates of birth and site location will not be included in the shared data set.

A Publications Committee appointed by the sponsor will review and approve all publications until the data is accessible to the public. No trial data may be presented or published without prior written approval of the Publications Committee. Final manuscripts prepared by members of the Publications Committee will be approved by the SMA Foundation before submission for publication. Detailed Publication Policies will be included in the Manual of Operations.

